#### Content Validity

The construction and validation of the knowledge, attitudes, and practice aspect of the questionnaire will be developed in alignment with the instrument development model [69]. The IPEC questions are validated and therefore do not require further validation.

Content validity will be achieved through review of the questionnaire by experts across varying health professionals from the targeted 5 discipline groups [70]. This is not a statistical test; yet, it aims to ensure the questionnaire explores the contextual issues [70]. This process will remain iterative, and the questionnaires will be adapted until each expert agrees on the final set of questions.

The scoring rubrics for the assessed scenarios in the pre- and postquestionnaire, will be developed in alignment with the WHO curriculum guidelines for training health care providers in responding to IPV [63]. Interrater consistency will be supported through assessor collaboration and the use of standardized scoring criteria. Interrater reliability will be measured through the kappa statistic to ensure that the data collected correctly measure the variable prior to the implementation of the project [71]. There will be 2 independent assessors who will grade all data requiring scoring through the rubrics. This process will be refined by piloting the rubric before implementation.

#### Test-Retest Reliability

The test-retest reliability method will be integrated into the implementation of the project to measure the reliability of the validated questionnaire [70,72]. A randomized subgroup of 20‐30 health professionals will be sought to volunteer and answer the questionnaire, and 2 weeks later, repeat the same questionnaire to determine the stability and replicability of the questions [73].

#### Sample Size

A minimum of 42 participants in total, from the 5 or more health professional groups will be recruited (midwives, social workers, medical staff, perinatal mental health nurse midwives, and Aboriginal Maternal and Infant Care workers). There will be several offerings of the simulation workshops conducted, due to the capacity of 10 participants in each session. To avoid bias, the program sessions will continue until all 5 health professional groups have been represented in the data collection.

#### Data Analysis

Descriptive and inferential statistics will be acquired through the pretest-posttest data collection questionnaires [74]. To determine the significance of perceived change post education, inferential statistics (paired *t* test and McNemar) will be used through the application of SPSS software (IBM SPSS Statistics; version 27).

Standard practice for reporting quantitative data includes detailing the baseline characteristics of participants; therefore, the protocol will report participant baseline characteristics descriptively (descriptive statistics) [75]. As attrition at the 4-month postintervention follow-up is anticipated, a table of baseline participant characteristics will be presented to allow comparison between participants retained in the study and those lost to follow-up [75]. This process thereby supports the assessment and analysis of potential attrition-related bias. To minimize missing data, questionnaires administered through REDCap (Research Electronic Data Capture; Vanderbilt University) will have the mandatory response settings enabled to reduce the risk of nonresponse bias [76]. Automated reminders regarding outstanding follow-up requirements will be sent to participants through the REDCap platform as a means of retention and tracking procedure recommendations [76].

The KAP survey will be structured to evaluate the knowledge, attitudes, and practices of participants. While the attitudes and practices are subjective self-reported changes, the knowledge-based questions will objectively measure the effect. Data that measure participant knowledge will be analyzed using the McNemar test, which is appropriate for paired categorical (dichotomous) data collected from the same participants pre- and postintervention. The McNemar test focuses on the discordant pairs to determine change for an individual participant over time [77]. Binary outcomes, with one categorical dependent variable (agree or disagree or true or false responses), will be compared to determine the effect, with *P* values calculated to assess the statistical significance [78]. The multiple-choice questions that are correct will receive a score of 1; incorrect and unsure will be scored 0 and will also be assessed at an item level using the McNemar test.

The IPEC tool and attitudes and practice Likert scale responses will be summed to generate a total score and domain-specific scores; higher scores indicate greater self-reported competency. The participant self-reported changes for each domain, and overall scores will be evaluated using a 2-tailed, paired *t* test to determine the mean and SD over time [78]. The Wilcoxon signed-rank test, however, will compare individual ordinal data for each Likert question to compare and determine the statistical significance.

The assessment of the video scenario questions will be scored in ordinal domains based on the rubrics and compared pre- and postinterventions using the Wilcoxon signed-rank test. The total rubric score will be analyzed through a paired *t* test.

Multiple comparisons arise from testing more than one outcome through different methods. Given the exploratory nature of the project, there will be no formal adjustment to multiple comparisons applied; instead, the results will be interpreted cautiously with consideration of the effect sizes and CIs. All data will be displayed in tables.

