### Phase 3: Evaluation

#### Overview

The evaluation of the ALIGN workshop will involve a single-group quasi-experimental pretest-posttest design (phase 3). The aim of phase 3 is to evaluate the perceived impact of the simulation-based interprofessional education intervention on health care professionals’ collaboration, knowledge, and behavioral responses to IPV disclosures during the perinatal period, addressing research question 4.

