#### Data Collection Tools

A pre- and postquestionnaire will be used to assess the knowledge, attitude, and practice changes of participants. The preworkshop questionnaire will establish a baseline; the postworkshop questionnaire will therefore measure immediate effects on participant knowledge, attitude, practice, and behavior [65]. There will be another follow-up questionnaire at the 4-month postintervention, that is designed to capture practice changes [66].

The questionnaire will be structured to evaluate the Knowledge (multiple choice and binary questions [true or false and yes or no]), Attitudes (Likert scale), and Practices (simulated video scenarios with rubric), referred to as the Knowledge, Attitudes, and Practices (KAP) framework. The KAP framework allows for the exploration of a population to assess knowledge (what is known), attitudes (what is believed), and practices (what is done) [65,67]. Additionally, these questions may identify knowledge gaps and behavioral patterns, aligning with the program’s goal of assessing the impact and informing future improvements [67]. The knowledge-based questions will be formulated at the conclusion of the phase 1 qualitative data collection.

To evaluate a change in collaborative practices, the evaluation of the program will integrate the validated 16-question IPEC competency self-assessment tool into the questionnaire [22,68]. This instrument provides a validated means of assessing interprofessional competencies by measuring the participants’ self-efficacy, in relation to the IPEC core competency framework [68]. The IPEC competency self-assessment tool is reliable and validated and can therefore be used to assess the development of the participants’ collaborative practice skills [68].

Changes in interprofessional practice will also be objectively assessed using predefined scoring rubrics, with standardized criteria applied to minimize interrater variability. This process will involve participants watching a simulated video, aligned with the program’s learning outcomes. The participants will be asked to provide a written response that will be graded using a standardized rubric before and after the intervention.

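### Attrition is expected at the 4-month follow-up, but only two-occasion paired tests are named, so the delayed change is at risk of bias that a three-occasion model could reduce

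*Protocol article*

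**What the plan says.** The Phase 3 Overview describes the design: "The evaluation of the ALIGN workshop will involve a single-group quasi-experimental pretest-posttest design (phase 3"). Data Collection Tools then sets three occasions. The first two are a baseline and an immediate post-workshop questionnaire. For the third: "There will be another follow-up questionnaire at the 4-month postintervention, that is designed to capture practice changes".

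The Phase 3 Data Analysis section names these inferential methods:

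- McNemar for knowledge items, worded as before versus after.
- A two-sided paired t test for summed IPEC, attitude and practice scores (totals and domains), worded more loosely as change over time, and a paired t test for the total rubric score.
- Wilcoxon signed-rank for single Likert items, and for the rubric domains, which are "compared pre- and postinterventions using the Wilcoxon signed-rank test".

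No sentence says which comparison the 4-month data enter, and no repeated-measures model or missing-data method is named.

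On attrition, the same section says: "As attrition at the 4-month postintervention follow-up is anticipated, a table of baseline participant characteristics will be presented to allow comparison" of those retained with those lost. It adds mandatory response settings and automated reminders in REDCap. Sample Size gives the planned number: "A minimum of 42 participants in total, from the 5 or more health professional groups will be recruited". No dropout rate accompanies it.

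**The concern.** The 4-month questionnaire is the only delayed measure, so any statement about lasting change rests on it. It is also where the protocol expects to lose people. A paired test comparing 4 months with an earlier occasion uses only participants who supplied both values. The immediate post-workshop score of a person who later drops out, which is already in hand and is likely to be informative about the missing result, plays no part.

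The stated measures do not fill that gap. A table of baseline characteristics can show that leavers differ, but it changes no estimate, and as worded it leaves out the immediate post-workshop scores. Mandatory fields prevent skipped items, not unreturned questionnaires. Reminders may reduce loss, but the protocol still expects attrition with them in place. With a single group, there is no between-group contrast in which selective loss might partly cancel.

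The plan relies on effect sizes and confidence intervals for cautious interpretation. Those are the quantities that selective dropout would shift.

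**Working it through.** **1. What the protocol gives.** A minimum of 42 participants, three occasions, paired tests, and attrition expected at an unstated rate. No inputs accompany the 42, so it cannot be reproduced. Back-solved for a paired t test (noncentral t, two-sided 5% assumed), 42 pairs give 80% power for d = 0.443.

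**2. Pairs left at 4 months** (42 × (1 − loss), rounded) and power at an assumed d = 0.5:

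| Loss | Pairs | d detectable at 80% | Power at d = 0.5 |
|---|---|---|---|
| 0% | 42 | 0.443 | 89% |
| 10% | 38 | 0.467 | 85% |
| 20% | 34 | 0.495 | 81% |
| 30% | 29 | 0.539 | 74% |
| 40% | 25 | 0.584 | 67% |
| 50% | 21 | 0.643 | 59% |

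This is the cost of losing people. It is context only and does not show what a different model would recover.

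**3. Bias by hand.** Assume 30% loss overall, 50% below and 10% above the median immediate gain, and a correlation of 0.6 between immediate and 4-month gain. The mean of a standard normal variable above its median is 0.798.

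- Mean standardized immediate gain among those retained: 0.798 × (0.9 − 0.5)/(0.9 + 0.5) = 0.228.
- Shift in the 4-month gain: 0.228 × 0.6 = 0.137 SD of that gain.
- With a 40%/20% split: 0.798 × (0.8 − 0.6)/(0.8 + 0.6) = 0.114, and 0.114 × 0.6 = 0.068 SD.

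**4. Bias by simulation.** Assumed: n = 42, score SD 1 at each occasion, correlation 0.6 between occasions, true changes from baseline of 0.50 (immediate) and 0.30 (4 months), and logistic retention with slope 1 per SD. The paired mean change among those with both values is compared with a likelihood-type estimate that uses all three occasions (4-month score regressed on the first two scores among those retained, then predicted for everyone). Bias in SD of the score:

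| Retention rises with | Method | 20% loss | 30% loss | 40% loss |
|---|---|---|---|---|
| nothing (random) | paired | 0.00 | 0.00 | 0.00 |
| baseline score | paired | −0.07 | −0.10 | −0.13 |
| baseline score | all data | 0.00 | 0.00 | 0.00 |
| immediate gain | paired | +0.08 | +0.12 | +0.15 |
| immediate gain | all data | 0.00 | +0.01 | 0.00 |
| unseen 4-month score | paired | +0.07 | +0.10 | +0.14 |
| unseen 4-month score | all data | +0.10 | +0.15 | +0.20 |

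**5. Units.** Step 4 is in SD of a single score. The SD of a change is √(2 × (1 − 0.6)) = 0.894, so 0.118 (immediate gain, 30% loss) is 0.118/0.894 = 0.13 SD of the change, close to the 0.137 in step 3.

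**6. Against sampling error.** With 29 pairs the standard error of a mean change is 1/√29 = 0.186 SD of the change. A shift of 0.137 is 0.137/0.186 = 0.74 standard errors. By normal approximation a nominal 95% interval then covers with probability Φ(1.96 − 0.74) − Φ(−1.96 − 0.74) ≈ 0.89. For a shift of 0.068 (0.37 standard errors) it is about 0.93.

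**The case against.** **The study does not rest on month 4.** This stands. A reader might infer that the 4-month questionnaire is the only measure of practice change. The text says otherwise: "A pre- and postquestionnaire will be used to assess the knowledge, attitude, and practice changes of participants"; "the postworkshop questionnaire will therefore measure immediate effects on participant knowledge, attitude, practice, and behavior"; and "Changes in interprofessional practice will also be objectively assessed using predefined scoring rubrics", before and after the workshop. The research question on behavioural response is therefore answered partly by data that attrition at 4 months does not touch. Month 4 is the only delayed measure, no more.

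**Bias is not shown.** Also right as far as it goes. A reader might infer that lasting change will be overstated. The protocol gives neither a dropout rate nor a mechanism. Under random dropout the bias is zero, and under dropout related to baseline score it understates the change. Only a risk is supported.

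**The analysis of month 4 is unspecified, and missing data are often left to an analysis plan.** Partly right: the protocol nowhere states that incomplete participants are excluded. But it does fix the tests, software, scoring and response to attrition. A plan that follows it inherits paired tests, and those use only people with both values.

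**The bias is smaller than one standard error.** True at 29 pairs. The interval nevertheless takes no account of it, so stated 95% coverage would be about 89–93% in the cases in step 6.

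**The mixed model can do worse.** True if dropout depends on the unseen 4-month score: +0.15 against +0.10 SD at 30% loss. The model's assumption must be stated and not treated as a cure.

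**Conclusion.** The point holds in a limited form. Three occasions are planned and attrition at the third is expected, yet the methods named use two occasions at a time and ignore the immediate scores of those lost. Reminders and mandatory fields are genuine measures against loss, so it would be wrong to say the table is the only response; but nothing stated adjusts the estimate.

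Under assumed loss of 20–40% related to baseline score or immediate gain, the 4-month change is off by about 0.07–0.15 SD in either direction. That is roughly a quarter to a half of the assumed true change of 0.30 SD (0.07/0.30 = 23%; 0.15/0.30 = 50%). An analysis of all three occasions brings this close to zero in those scenarios. Every figure depends on the assumed rate, mechanism, correlation and true change; none comes from the protocol.

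The study is exploratory and evaluates perceived impact, and no confirmatory 4-month claim is made. The change is worth making before data collection, but the study does not fail without it.

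**What to change.** In the Phase 3 Data Analysis section:

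1. State which outcomes are repeated at 4 months and which contrast they enter.
2. For summed scores collected at all three occasions (IPEC and attitude/practice totals and domains), use a linear mixed model with time as a three-level factor, a within-participant covariance (unstructured is feasible with three occasions) and all observed data. Report post-minus-pre and 4-month-minus-pre contrasts with 95% CIs. Keep the paired t test as a sensitivity analysis.
3. Include the rubric total only if the video scenario is repeated at 4 months; the protocol describes it only before and after the workshop.
4. Keep knowledge at item level, as planned; no knowledge total is stated. If items are analysed at 4 months, the counterpart is a binary repeated-measures model or multiple imputation.
5. Add immediate post-workshop scores to the retained-versus-lost table.
6. State that the model assumes data are missing at random and does not repair dropout that depends on the unseen 4-month score. A sensitivity analysis shifting the missing 4-month values would show how much this matters.

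The cost is wording. The planned SPSS software has a MIXED procedure, and items 2 and 5 need no new data for scores already repeated at 4 months. The drawbacks are a somewhat less familiar method and an assumption that the data cannot verify.

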### Objectives

The objectives of the study are as follows:

To design and develop a simulation workshop for health professionals that captures the experiences of women with lived experience of IPV in pregnancy in addition to addressing the needs of health professionals providing that care.To evaluate the perceived impact of the simulation workshop to determine the changes in the health professional’s collaboration and behavioral response to IPV disclosures and ongoing management of care throughout the perinatal context.To evaluate changes in participants’ objective knowledge related to recognizing and responding to IPV disclosures during maternity care following a simulation-based interprofessional education intervention, using standardized pre- and postintervention knowledge measures.To evaluate changes in participants’ interprofessional responses to simulated IPV disclosure scenarios, using standardized assessment that is scored with predefined rubrics before and after the intervention.

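### Objective 3 (change in knowledge) has only item-by-item McNemar tests and no total score, so the plan gives no overall estimate of knowledge change

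*Protocol article*

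**What the plan says.** The third objective (Objectives section) concerns change in "objective knowledge related to recognizing and responding to IPV disclosures during maternity care", measured before and after the workshop.

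For these data the Phase 3 Data Analysis section names one test: "Data that measure participant knowledge will be analyzed using the McNemar test, which is appropriate for paired categorical (dichotomous) data". True/false and agree/disagree responses are compared as binary outcomes with P values. For multiple-choice questions a correct answer scores 1; "incorrect and unsure will be scored 0 and will also be assessed at an item level using the McNemar test".

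The other scales are treated differently in the same section: "The IPEC tool and attitudes and practice Likert scale responses will be summed to generate a total score and domain-specific scores". Those scores go into a two-tailed paired t test. The video rubric also has a total analysed by paired t test, with its ordinal domains compared by Wilcoxon signed-rank test.

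On multiplicity, the section says "there will be no formal adjustment to multiple comparisons applied". It gives the exploratory nature of the project as the reason and promises cautious interpretation using effect sizes and CIs.

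On size, the Sample Size section says "A minimum of 42 participants in total, from the 5 or more health professional groups will be recruited". It gives no effect size, alpha or power. The number of knowledge items is also not given, because Data Collection Tools says they will be written after phase 1.

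**The concern.** The objective is about participants' knowledge, but the planned analysis works only on single questions. A McNemar test compares the group's proportion correct on one item before and after. It does not measure how much a participant's knowledge changed, although the Data Analysis section describes it as showing change for an individual participant. No knowledge total, domain score or key item is named, and no rule turns the item results into an answer to objective 3.

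If some items reach P<.05 and others do not, the report can stress either group. The promised cautious reading of effect sizes and CIs has no overall knowledge effect to work on. The convergence matrix planned under Triangulation of Findings would likewise have no single knowledge result to code as agreement or dissonance.

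**Working it through.** **1. How each phase 3 measure is analysed (Data Analysis section)**

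| Measure | Item or domain level | Total |
|---|---|---|
| IPEC | Wilcoxon per item; paired t per domain | paired t |
| Attitude and practice Likert items | Wilcoxon per item; paired t per domain | paired t |
| Video rubric | Wilcoxon per domain | paired t |
| Knowledge | McNemar per item | none |

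Knowledge is the only measure without a total, although its multiple-choice items are already scored 1/0.

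**2. Inputs for the size of the problem**

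From the document: n = 42 pairs (the stated minimum). The document gives no power calculation, so there is no figure of its own to reproduce. Assumed: two-sided alpha 0.05; the proportions moving from wrong to right (a) and from right to wrong (b); 15 or 20 items; the inter-item correlation of change (ρ).

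**3. Power of one exact McNemar test**

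The number of discordant pairs is m ~ Binomial(42, a+b). Given m, the wrong-to-right count is Binomial(m, a/(a+b)), and the test rejects when the two-sided binomial P against 1/2 is at most .05. Power is the sum over m.

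| Net gain | b = 5% | b = 10% |
|---|---|---|
| 10 points | 19% | 14% |
| 15 points | 39% | 29% |
| 20 points | 60% | 46% |
| 25 points | 77% | 63% |
| 30 points | 88% | 77% |
| 40 points | 98% | not computed |

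For 80% exact power the net gain must be about 26 points if b = 5%, or 32 points if b = 10%. The mid-P and asymptotic versions are somewhat more powerful (for example 49% instead of 39% at 20%/5%).

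**4. Power of a total score on the same data**

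Take 15 items, of which k improve by 15 points (a = 25%, b = 10%). The variance of change per item is v = 0.35 − 0.15² = 0.3275, kept the same for all items. The standardised change of the total is

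d = k × 0.15 / √(15 × v × (1 + 14ρ)).

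For k = 15 and ρ = 0.1, d = 2.25 / √(4.9125 × 2.4) = 2.25 / 3.434 = 0.66. Paired t power at n = 42 comes from the noncentral t distribution.

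| ρ | All 15 improve: d | Power | 8 of 15 improve: power |
|---|---|---|---|
| 0.1 | 0.66 | 99% | 60% |
| 0.2 | 0.52 | 91% | 42% |
| 0.3 | 0.45 | 80% | 32% |
| 0.4 | 0.40 | 71% | 27% |

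The matching power for one item is 29%. With a uniform gain the total does much better. If about half the items improve, the advantage is modest at low ρ and gone at ρ = 0.4.

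**5. Chance findings across items**

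With 20 independent items and no true change, the chance of at least one P<.05 is 1 − 0.95²⁰ = 64% at nominal size. The exact test is conservative: its size at n = 42 is 0.6%, 2.0% or 2.5% when 10%, 20% or 30% of pairs are discordant. That gives 11%, 33% or 40% over 20 items.

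**The case against.** Several points on the other side stand.

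- **Item tests do evaluate change.** A reader might infer that nothing in the plan addresses objective 3. That goes too far: paired item tests show change on individual questions. What is missing is a summary of overall change.
- **Poor power is not a fact of the document.** A reader might infer that every item test is badly underpowered. The protocol states no effect size or discordance rate, and the questionnaire is given immediately after a workshop, so gains of 25 points or more cannot be excluded. With 5% losing, power at such gains is 77% or higher.
- **Non-adjustment is declared.** The exploratory rationale is explicit and not an error in itself. It does not supply an overall knowledge effect for the cautious reading to use.
- **Knowledge is not the only objective measure.** Data Analysis contrasts objective knowledge with self-reported attitudes and practices, which could suggest that it is. Data Collection Tools says practice is also objectively assessed, by rubric, and that measure has a total.
- **A total can hide concentrated gains.** If teaching works on a few topics only, item results show where. The protocol wants to identify knowledge gaps, so item results deserve to be kept.

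One might also read "will also be assessed at an item level using the McNemar test" as implying a total alongside the item tests. If so, that total is neither defined nor given a test. Nor is this a detail left to a fuller plan: the article itself fixes the scoring, the test and the level of analysis.

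**Conclusion.** The point holds in a limited form. Objective 3 has no planned estimate or CI of overall knowledge change, while every other phase 3 scale has a total with a paired t test. This follows from the protocol's text and needs no assumption.

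The size of the statistical loss is conditional. At n = 42 and an assumed two-sided 5% level, single-item exact power is 14% to 60% for gains of 10 to 20 points, 63% to 77% at 25 points, and 77% to 98% at 30 to 40 points. A 15-item total has 71% to 99% power for a uniform 15-point gain with ρ from 0.4 to 0.1, but only 27% to 60% if 8 of 15 items improve. The case for a total rests mainly on giving the objective one interpretable answer. The gain in power is a likely benefit that depends on gains being spread across items.

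**What to change.** In Data Analysis, name the total knowledge score (number or percent correct, with unsure scored 0) as the analysis for objective 3. Report its mean change with a 95% CI, using the paired t test already planned for the other totals. Keep item-level before/after percentages as supportive, descriptive results showing where knowledge changed.

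This changes wording only and needs no extra participants or data. The items are not yet written, so the total can be specified before any phase 3 data exist. The costs are that single-item P values no longer carry the conclusion, and that a total can dilute gains confined to a few items, which the item table would still show.
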